## Abstract

**Background:**

Few children achieve the recommended daily levels of physical activity. Active school transportation (AST) offers a valuable opportunity to increase children’s physical activity. Initiatives promoting AST in early childhood are important and have the potential to reverse the decline in physical activity.

**Objective:**

This study protocol outlines an age-cohort design to evaluate the effectiveness of the Sustainable Innovation for Children Transporting Actively (SICTA) intervention on children’s AST.

**Methods:**

SICTA is a 4-week school-based intervention that incorporates gamification elements to enhance motivation and aims to increase AST in children. The intervention involves children and their parents as gatekeepers, as well as teachers delivering the intervention. All children, parents, and teachers in all schools, from grades 4 to 6 in one municipality in the southern part of Sweden, will be invited to participate in the evaluation. Following the age-cohort design, students at baseline (late fall 2024) will be compared with students of the same age from the same schools 1 year later at follow-up (late fall 2025) after receiving the intervention (implemented in late fall 2025). Using questionnaires at baseline and follow-up, this study will examine the effects of the intervention on children’s levels of AST. Children’s independent mobility and several mediators related to AST in both children and parents, based on the theory of planned behavior, the transtheoretical model of change, and self-determination theory, will also be examined. The intervention will also be evaluated from a sustainable perspective using the sustainable value equation. At follow-up, data collection will include a questionnaire for teachers assessing the feasibility of the intervention.

**Results:**

The project is funded for the period 2024-2026, and follow-up data collection is ongoing following completion of the intervention in late fall 2025. Results will be reported according to the predefined outcomes, including changes in AST, children’s independent mobility, psychosocial determinants among children and parents, and sustainability outcomes, as well as feasibility.

**Conclusions:**

The findings are expected to provide valuable insights into the effectiveness of the SICTA intervention, facilitating knowledge dissemination among end users and policymakers.

**Trial Registration:**

Swedish National Research Database Researchweb.org 283668; https://tinyurl.com/496rc6r4

**International Registered Report Identifier (IRRID):**

DERR1-10.2196/92946

## Introduction

### Background

Physical activity is essential for the well-being of children and adolescents [1]. Despite its importance, the majority of children and adolescents globally do not meet the recommended 60 minutes of physical activity per day [2]. In addition, disparities in physical activity levels and related health outcomes persist across populations, with children from less socially advantaged backgrounds being less likely to engage in regular physical activity [3,4]. This highlights the essential role of schools as a key setting for health promotion, providing equitable access to interventions that reach children across all socioeconomic backgrounds [5]. Furthermore, active school transportation (AST), typically involving walking or cycling for all or part of the transport to and from school, can make a significant contribution to a child’s total daily physical activity [6,7]. Additionally, previous research has suggested that AST is positively associated with cardiovascular fitness, academic performance, safer traffic environments, reduced air pollution, and lower greenhouse gas emissions [8-11]. In addition, children’s independent mobility (CIM), defined as the ability of children to move around freely without adult supervision, has been shown in previous studies to be an important facilitator of increased physical activity and AST [12-14]. Thus, promoting AST and CIM has the potential to address important societal challenges and contribute to several Sustainable Development Goals (SDGs) in the United Nations 2030 Agenda [15]. However, in many Western countries, there has been a marked decline in the prevalence of AST as well as CIM during the last few decades [16-19]. Nevertheless, recent trends indicate that the decrease might be leveling off somewhat [20]. However, there is still great potential to increase AST as a means of promoting physical activity levels in children [20]. Additionally, as physical activity behaviors, such as AST, are often established in childhood and persist into adulthood, health-promoting initiatives should be introduced early in life [21,22]. Moreover, although several initiatives have been launched to address AST, evidence-based and scalable solutions remain scarce. Systematic reviews indicate that interventions can increase AST among children and adolescents; however, the studies vary widely, and the quality of evidence is generally low [23,24]. High-quality research using behavior change theories as a basis for intervention design, as well as robust evaluation methods and reliable measurement instruments, is needed to better understand AST and assess intervention effectiveness.

### Sustainable Innovation for Children Transporting Actively: Development of the Intervention

The research project Sustainable Innovation for Children Transporting Actively (SICTA) was formed as a 4-week school-based intervention initially developed in 2016 in Sweden [25]. The SICTA intervention is based on theory, with 3 main concepts: social cognitive theory, empowerment, and gamification. Social cognitive theory involves factors related to AST behavior, including knowledge, self-efficacy, outcome expectations, short- and long-term goals, facilitators, and impediments to change. Moreover, empowerment facilitates the involvement of end users—children, teachers, and parents—in outlining the intervention. Gamification, which is the use of game design in a nongame context, is used to motivate children to participate in the intervention and perform assignments that are applicable to their route to school. The assignments are integrated into the curriculum; for example, one assignment could involve counting people and animals encountered during AST and analyzing these data in math classes. A long-term goal is also to track the number of kilometers walked and cycled by the class during the project. Thus, in line with the idea of gamification, when completing assignments, children receive rewards when they are accomplished. The intervention consists of 5 different steps: engaging parents through a parental meeting, increasing children’s knowledge of active transport, preparing weekly assignments for the children, encouraging walking and cycling to school over 4 weeks, and finally celebrating their achievements. At the parental meeting, parents are provided with information about the intervention, its benefits for AST, and an opportunity to discuss any concerns or perceived risks. To support teachers, they have access to an online platform called the Teacher’s portal. The assignments developed in the portal use innovative, game-based, student-centered pedagogical approaches that are integrated into contemporary school curricula. The criteria used during the development process included ensuring that the activities had a scientific foundation in educational research, an explicit connection to syllabi, opportunities for student influence, and the incorporation of peer collaboration. Therefore, it is evident from the previous description that the SICTA intervention is complex, involving multiple components and requiring skills from both the deliverers and the recipients [26]. Its complexity also arises from the flexibility of the intervention’s components and delivery, as well as the dynamic interactions between the intervention, its context, parents, children, and teachers. This adaptability ensures alignment with each school’s unique structure and functionality. In addition, guidelines stress the importance of considering both the intervention’s components and their interactions with the environment [26].

### SICTA: Previous Research

Since its initial development, SICTA has been continuously refined and evaluated, primarily through qualitative studies that focus on the perspectives of children, parents, and teachers [27-31]. These studies revealed that the intervention has received positive feedback from children, teachers [27,29,30,32], and parents [28,31], and a long-term qualitative follow-up showed that it fostered a habit of using AST among participants [30]. In 2020, the SICTA research project advanced to the next phase, SICTA 2.0, and feasibility evaluation continued. Qualitative evaluations have shown that teachers find the intervention flexible, meaningful, and easy to implement [32]. To summarize, the research around this project has led to an understanding of three key values, encapsulated by the acronym “FIT,” for different groups of end users: (1) it is a *fun* intervention for the children, (2) it *inspires* peace of mind for the parents, and (3) it is *teacher friendly*.

Moreover, in 2022, a nonrandomized controlled pilot study was conducted to assess the feasibility of the evaluation design, with a mix of qualitative and quantitative data [33]. The results highlight the complexity and challenges of conducting controlled research among school children. Although children were positive about participation and found reporting to be easy, our results invoke the need to use alternative evaluation designs and recruitment strategies that attract children using all modes of travel when evaluating AST interventions in school contexts. Using schools as the intervention arena allows almost all children to be reached, addressing inequities in physical activity and health [34]. However, schools are complex environments where randomized controlled trials (RCTs) are challenging [35]. Our pilot study showed low participation willingness and dissatisfaction among control school children, suggesting that an RCT is not suitable for a full-scale evaluation [33]. However, an age-cohort design has been proposed as a more feasible approach for evaluating interventions within a school setting [35].

In summary, this study protocol outlines an age-cohort design [35] to evaluate the effectiveness of the SICTA intervention on children’s AST. It also involves evaluating the intervention from a sustainable perspective. More specifically, the study addresses the following research questions: (1) How does the school-based intervention SICTA influence children’s active transportation to and/or from school? (2) How does the intervention influence CIM? (3) Which psychosocial aspects and sociodemographic characteristics are related to AST among children and parents? and (4) Can a sustainable value equation be applied to assess the sustainable value of the intervention?

## Methods

### Study Design

An age-cohort design will be applied to evaluate the effectiveness of the SICTA intervention on children’s AST [35]. In an age-cohort design, same-age students within the same schools are compared over time (Figure 1). For example, students in fifth grade at baseline (T_0_) will be compared with students in fifth grade from the same school at follow-up (T_1_) 1 year later. With such a study design, possible age-related maturational differences between the comparison groups are controlled. The SICTA intervention is evaluated using this age-cohort design, where students at baseline (late fall 2024) will be compared with same-aged students from the same schools 1 year later at follow-up (late fall 2025) after receiving the intervention (implemented in late fall 2025). The study was registered in the Swedish national research database Researchweb (project 283668) on October 25, 2024.

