### Study Sample

In collaboration with the municipality involved in the project, public schools involving grades 4 to 6 will be identified, and invitations will be sent to principals to participate. Upon acceptance of participation by school principals, all children in grades 4 to 6, along with their parents and teachers at the participating schools, will be invited to participate in the study.

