### Data Collection and Measurements

For all the research questions, data will be collected from the children and their parents at 2 time points, baseline (T_0_) and follow-up (T_1_). In addition, data will be collected from teachers at follow-up (T_1_). Multimedia Appendix 1 provides an overview of the data collection, including instruments used at baseline and follow-up. A detailed description of data collection and analysis is provided in the following sections for each research question. The baseline data collection is planned to be performed during 2 weeks in late fall 2024, and the data collection following the intervention is planned to be performed exactly 1 year later, 2 weeks after the 4-week SICTA intervention has ended, in line with the age-cohort design (Figure 1).

### Research Question 1

The number of weekly active school transports (0-10) will be collected using the wASTapp [36]. The wASTapp is a web-based form developed to enable daily self-reports of transportation mode, time, and distance and has shown satisfactory criterion validity when tested in children in grades 4 to 6. In the wASTapp web-based form, children are able to report their daily transport either in the classroom guided by their teachers (using school computers) or on their own phones. Children who report via their phone will receive a daily SMS text message containing a link to the web-based form. If children lack access to a school computer or mobile phone for completing self-reported questions, paper-based reporting will be provided as needed.

### Research Question 2

Data on CIM will be collected using the CIM License questionnaire [37]. The questionnaire consists of 6 questions with “yes” and “no” answer options and assesses the level of independent mobility in children.

### Research Question 3

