### Data Analysis

#### Quantitative Analysis

For all research questions, descriptive statistics will be used to summarize the data. Categorical variables will be reported as frequencies and percentages, and continuous variables will be reported as means and SDs or medians and IQRs, depending on distributional characteristics. Before the main analyses for research questions 1 to 3, the design effect will be evaluated to account for clustering within schools. Specifically, the intraclass correlation coefficient will be estimated for each outcome using an unconditional linear mixed-effects model with school as a random intercept [44]. For research questions 1 to 2, the data (wASTapp and CIM) are planned to be treated as continuous outcomes, as the wASTapp measure is based on a 0 to 10 scale and the CIM variable will be operationalized as an index ranging from 0 to 6, derived from 6 items. Changes from baseline (T_0_) to follow-up (T_1_) will be analyzed using an analysis of covariance, with T_1_ as the dependent variable and T_0_ included as a covariate. The models are planned to be adjusted for sociodemographic characteristics. For research question 3, associations between psychosocial factors, sociodemographic characteristics, and AST will be analyzed using analysis of covariance, with AST at follow-up (T_1_) as the dependent variable and baseline values (T_0_) included as a covariate. For all research questions (1-3), model assumptions will be assessed, and the final choice of regression model will be guided by the distribution of the outcomes. Although the outcomes are planned to be treated as continuous, alternative approaches (eg, ordinal models) will be considered if this is not supported by the data [45]. If clustering within schools is present, corresponding mixed-effects models will be applied. Missing data will be examined for extent and patterns [45]. If missing at random is considered plausible, multiple imputation will be used. Sensitivity analyses will include complete case analyses to assess robustness. A significance level of .05 will be applied. All analyses are planned to be conducted using SPSS (version 31; IBM Corp).

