Our previous results highlight the complexity and challenges of conducting controlled research among school children [33]. Given these challenges, we have chosen an age-cohort design [35] to evaluate the SICTA intervention. This approach is particularly well suited for studying school-based interventions, as it allows for the examination of developmental changes over time while maintaining the feasibility needed for real-world implementation [46,47]. Age-cohort designs offer several advantages in this context. By following different age groups as they progress through school, this method enables a longitudinal perspective on intervention effects without requiring random assignment [35,47]. This not only improves practical feasibility but also minimizes issues such as ethical concerns, interference, and contamination—challenges often encountered in school-based studies [47]. In a previous pilot RCT of the SICTA intervention, significant participant attrition due to study design constraints further underscored the need for a more adaptable approach [33]. Additionally, age-cohort designs align well with the practice-based evidence framework, which is increasingly emphasized in public health research [46]. Many school-based interventions are implemented as natural experiments, making it essential to adopt methodologies that reflect real-world conditions rather than rigid experimental controls. By using an age-cohort design, we can capture broader trends within the school context while enhancing the generalizability of our findings [47]. However, given the pragmatic age-cohort design and real-world implementation, the findings should be interpreted as reflecting changes associated with the intervention rather than causal effects. In line with the Medical Research Council framework for complex interventions, effectiveness in this study refers to the extent to which the intervention may produce intended outcomes under real-world conditions, acknowledging contextual variability and implementation flexibility [26].

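### Up to two thirds of eligible children fall in both waves; a same-age comparison pooled over grades, with school as the only dependence term, would report too large a standard error

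*Protocol article*

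**What the plan says.** Four parts of the protocol article bear on this.

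- **Who is measured.** Under Study Sample, "all children in grades 4 to 6, along with their parents and teachers at the participating schools, will be invited to participate in the study". Under Data Collection and Measurements, "the data collection following the intervention is planned to be performed exactly 1 year later".
- **What is compared.** Study Design sets the general contrast: "students at baseline (late fall 2024) will be compared with same-aged students from the same schools 1 year later at follow-up (late fall 2025". It then illustrates this for one grade: "students in fifth grade at baseline (T_0_) will be compared with students in fifth grade from the same school at follow-up (T_1_) 1 year later".
- **How the design is described later.** Expected Contributions says: "By following different age groups as they progress through school, this method enables a longitudinal perspective on intervention effects without requiring random assignment".
- **How dependence is handled.** Under Quantitative Analysis, the intraclass correlation is estimated "using an unconditional linear mixed-effects model with school as a random intercept", and then "If clustering within schools is present, corresponding mixed-effects models will be applied". Change is analysed by ANCOVA, with the T1 value as outcome and the T0 value as covariate. No child-level or parent-level term is named.

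**The concern.** With the same three grades invited in the same schools a year apart, most eligible children belong to both waves, one grade higher the second time. The same holds for their parents. The analysis section provides for this in only one way, through the T0 covariate in the ANCOVA. That model needs two values per child and compares each child with itself a year older, whereas Study Design asks for same-age groups a year apart. Once the same-age contrast is fitted, the only dependence term on offer is school.

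Precision is at stake. If repeated children are treated as different children, the standard error of the year effect is overstated, and a real increase in active transport could be reported as no clear effect.

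**Working it through.** The article states no sample size, power, standard deviation or correlation, so there is no figure of its own to reproduce. The within-child correlation and the overlap among respondents are assumptions, shown as ranges.

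**Step 1. Overlap.** Inputs are grades 4, 5 and 6 in both years and a one-year gap. T0 grade 4 becomes T1 grade 5, and T0 grade 5 becomes T1 grade 6. With equal grades and no moves, f = 2/3 of those eligible at T1 were also eligible at T0. If a share p takes part in each wave independently, the share of T1 respondents also seen at T0 is (2/3)p: 60%, 47% and 33% for p = 90%, 70% and 50%.

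**Step 2. Variance of the pooled same-age contrast.** Give each of the six grade-by-year cell means variance 1 (given school, with school effects stable over the year). Let r be the one-year within-child correlation given school. The grade-balanced year effect is the sum over grades of (T1 minus T0), divided by 3.

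- Repeated children ignored: 6/9 = 0.667.
- Full overlap: two pairs of cells (T0 grade 4 with T1 grade 5, T0 grade 5 with T1 grade 6) have covariance r, so the variance is (6 − 4r)/9. This is 0.533, 0.444 and 0.356 for r = 0.3, 0.5 and 0.7.
- In general, true variance divided by reported variance is 1 − f·r, and the reported standard error is too large by k = 1/√(1 − f·r).

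**Step 3. Size and consequence.** For a two-sided nominal 0.05 test, actual type I error is 2(1 − Φ(1.96k)). Power that would be 80% with a correct standard error is Φ(2.80 − 1.96k).

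| Overlap f | r | k | Actual type I error | Power instead of 80% |
|---|---|---|---|---|
| 2/3 | 0.3 | 1.12 | 0.028 | 73% |
| 2/3 | 0.5 | 1.22 | 0.016 | 66% |
| 2/3 | 0.7 | 1.37 | 0.007 | 55% |
| 1/3 | 0.3 | 1.05 | 0.039 | 77% |
| 1/3 | 0.5 | 1.10 | 0.032 | 74% |
| 1/3 | 0.7 | 1.14 | 0.025 | 71% |

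**Step 4. Check by simulation.** The set-up was 12 schools, 30 children per grade, school intraclass correlation 0.05, full overlap, 300 runs, and a mixed model with year, grade and a school intercept (all assumed values). Mean model standard error over empirical standard deviation was 1.28 at r = 0.5 and 1.35 at r = 0.7, with type I error 0.02 and 0.01. This agrees with Step 3 within simulation error. For grade 5 alone the ratios were 1.03 and 1.02, so a single-grade contrast has about the right standard error.

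**Step 5. What a child term changes in the estimate itself.** The generalised least squares variances are 0.531, 0.438 and 0.343, against 0.533, 0.444 and 0.356 for the unweighted contrast. The gain is 0.5%, 1.6% and 3.5%. Nearly all the benefit lies in reporting the right standard error.

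**The case against.** The strongest reply is that the article nowhere specifies a stacked two-wave model. It specifies an ANCOVA, whose T0 covariate does handle within-child dependence for children seen twice. Its one worked example, fifth grade against fifth grade, shares no children apart from repeaters. Random-effects structure is often left to an analysis plan, and the article keeps the final regression model open.

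Much of this stands. The point is conditional on fitting the same-age contrast pooled over grades. It remains because the ANCOVA does not estimate that contrast, and the article itself fixes school as the dependence term. The choice it leaves open is tied to the distribution of the outcome, with a mixed model conditional on school clustering only.

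A reader might infer four stronger things that the documents do not support.

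- **That two thirds of respondents are the same children.** Two thirds is the ceiling for eligible children. The article gives no participation figures.
- **That the plan presents two disjoint samples.** Study Design never says so, and Expected Contributions speaks of age groups followed through school.
- **That a positive result would be unsafe.** Ignoring positive within-child correlation makes the pooled test conservative.
- **That nearly half the information is thrown away.** At r = 0.7 the reported variance is 0.667 against a true 0.356, so the true variance is 47% lower. That describes an overstated report. By Step 5 the estimator itself is almost fully efficient.

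**Conclusion.** The concern holds in a limited form. The two waves share up to two thirds of eligible children, and the analysis section has no child-level term for the same-age contrast that the design calls for. Pooled over grades with school only, that contrast would carry a standard error 1.12 to 1.37 times too large at full overlap, or 1.05 to 1.14 times at half that overlap. The cost is power; this error alone does not inflate false positives.

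The figures assume equal grade sizes, equal variances, school effects stable across the two years and r between 0.3 and 0.7. Other sources of dependence, such as class, are left aside. The overlap itself follows from the invited grades and the one-year gap. It is a matter of correct error bars, worth settling when Study Design and Quantitative Analysis are brought into line.

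**What to change.** - **Main model.** Stack both waves, with year, grade and school, and add a child random intercept or child-robust standard errors. Do the same for parents. The written ANCOVA already requires each child's T0 and T1 values to be linked, so a pseudonymous key should be no new demand.
- **Sensitivity analysis.** Prespecify grade 4 at T0 against grade 4 at T1. These groups share no children (repeaters aside) and neither has been measured before, whereas T1 grades 5 and 6 were invited to answer the same instruments a year earlier. No linkage is needed.
- **If no key was kept at baseline.** Report grade-specific contrasts, or a school-level paired analysis in which each school's change between years is the unit. Do not average the grade-specific results as if they were independent, because that brings back the error.

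**Cost.** One more model term and small data-management work. Follow-up collection is described as ongoing, so the key should be checked now. The sensitivity and fallback analyses are less precise. In the units above, a single-grade contrast has variance 2, so its standard error is √(2/0.533) = 1.9 to √(2/0.356) = 2.4 times that of the pooled contrast at full overlap. The paired analysis depends on the number of schools, which the article does not give.
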